**Figure 1 figure1:**
[figure not shown]
Study design and workflow of work packages (WPs). RCTs: randomized controlled trials.

### Recruitment

A large part of the study will run throughout the course of a worldwide pandemic, with the accompanying societal restrictions setting the context of the project. Most of the data collection will take place digitally, with reduced need for travel and physical meetings, using online surveys, video interviews, and interactive methods (eg, stakeholder analyses and workshops). The study population will include both experts and representatives from the general public as part of a holistic approach to how health risk and consequences are understood and communicated on all levels. More detail about the individual WPs is provided in the following sections.

### Phase 1: Establishing What Needs to Be Communicated (WP1)

WP1 will apply multiple qualitative methods to identify communication strategies and key topics related to pandemic risks to be communicated to the public. The views from both communicators and receivers of pandemic information are included. WP1 will inform WP2 and WP3 on what people already know, how they make decisions, and what they need to know to make more informed decisions when facing pandemic risks [32,34].

#### Rapid Scoping Review

The WP will involve a rapid scoping review [36,37] to obtain an overview of the evidence pertaining to diverse modes of communication used by health authorities in health risk communication with the public during a pandemic. The databases MEDLINE and EMBASE will be searched for publications from 2009 to 2020. This will provide information about key scientific concepts, types of outcomes, and research gaps related to diverse modes of communication.

#### Mental Models

Employing semistructured individual interviews, WP1 will involve the creation of 2 mental models. First, a public mental model will explore how the public perceives difficult scientific concepts and acts on the public health risk communication related to COVID-19. Second, an expert mental model will identify key topics and communication strategies related to pandemic risk [32]. Analyses will be guided by the mental model framework by de Bruin and Bostrom [34]. Mental models are representations of how something works in the real world, and the framework by de Bruin and Bostrom [34] was developed to assess what to address in science communication.

Rather than recruiting a large representative sample, it is recommended to recruit a small but diverse sample of participants (~10-15 participants) when exploring mental models [34]. For the public mental model, we apply a purposive sample of Norwegian citizens between 18 years and 80 years old, with various levels of education, gender, and a range of geographic regions in Norway. For the expert mental model, we include experts with various levels of knowledge of issues regarding COVID-19 risk and mitigation at different system levels (eg, municipality, hospital, national level, research). The identified topics will be analyzed in a directed content analysis, focusing on scientific concepts for public risk communication and the identification of possible new scientific concepts for pandemic risk communication [38].

#### Stakeholder Analysis

Finally, in WP1, we will undertake a stakeholder analysis to identify various stakeholder groups, assessing their different roles and values [39]. This to gain insight into the responsibility of different stakeholder groups, the perspectives of those involved in public health risk communication, and possible trade-offs in public risk communication. Here, we define stakeholders as individuals who represent a unit or organization that participates in public risk communication related to COVID-19 in Norway.

First, we will identify key stakeholder groups for pandemic risk communication at the local municipal level, at the hospital level, and at the policy level by reviewing publicly available policy documents describing the stakeholder’s roles and responsibility in pandemic management. Our sampling strategy is to include stakeholders with key roles in risk communication across these levels in the health care system. We then assess their different perspectives and values by interviewing a sample of ~10 stakeholders involved in communication of pandemic risk information representing different system levels. The document and participant interview data will be analyzed in a directed qualitative content analysis with predetermined categories for micro, macro, and meso levels and inductive category development to analyze values and perspectives [40]. Here, micro-level research refers to the examination of individuals and individual-level interactions (eg, intentions, feelings, and beliefs), the meso-level examines groups (including teams, units, and organizations), and macro-level research examines the political-administrative environment (including national systems, regulation, and cultures).

#### Recruitment and Sampling

User representatives, nongovernmental organizations, partners in the consortium from Stavanger University Hospital, Haukeland University Hospital, and the Center for Developing Institutional and Home Care Services Sogn and Fjordane will contribute to the recruitment in the various WP1 substudies. Participants will also be recruited by inviting eligible participants identified by the COVCOM team.

### Phase 2: Creating Communication (WP2)

Creative choices are central to filmmaking but are rarely considered when communicating science. In this WP, we will study the creative processes that underlie effective translation of scientific information into understandable communication.

#### Video Review

To explore how videos created by health authorities measure up to contemporary video content, WP2 will include a video review of existing COVID-19 video communication. Online sites for Norwegian health authorities, including health entities at both national and regional levels, will be searched for video content, and entities with a dedicated YouTube channel featuring COVID-19–related video content will be included. These videos will be compared with COVID-19–related videos created by the WHO, as well as the most watched COVID-19 videos on YouTube. Aiming for a comparable number of videos, we will select, for example, the top 10 to 20 videos on YouTube for each of the search terms “covid 19” and “corona virus” using the YouTube search engine. Press briefings, live videos, and news reports will be excluded: We are interested in purposely produced video content rather than mere recordings of ongoing events. A content analysis of video formats and creative means utilized will be carried out to identify how health authorities measure up to contemporary video communication, both creatively and in reaching video consumers, identifying potential shortcomings and potential for improvement.

#### The Communicators’ Views

Aiming to uncover structural differences and similarities in how communicators from different fields approach the creation of health science communication, we will recruit 2 participants from each of 6 different professions: public health communication, health communication, science TV and film production, video journalism, creative advertising, and social media. First, we will conduct semistructured individual interviews, identifying their approaches to video communication, their thoughts on existing COVID-19 videos, and their take on interdisciplinary collaboration. Participants will then be paired profession-wise and observed while discussing ideas for new pandemic-related video communication. Through content analysis gaps and differences in the weighting, sequencing and overall approach when tasked with creating pandemic video communication will be identified.

#### Turning Scientific Information Into Accessible Videos

Informed by WP1, professional audiovisual science communicators will create videos with explanations of key topics related to pandemics aimed at laypersons. This entails a focus on factors like choice of sender, ethos of the messenger, semantics, properties of context, metaphors, use of props, visual language, cinematic techniques, and editing. The output will be multiple research-based videos developed to translate pandemic scientific information in different ways, ready for experimental testing and assessment of the effect of creative choices on outcomes related to learning and attitudes toward the topic (in WP3).

This creative work will be observed, with an estimated 10 group sessions involving 1 hour of creative concept development and 10 hours of observation of the production, supplemented with 10 half-hour individual interviews. These time estimates are pragmatically chosen as estimates of how much—and how closely—the creative process and the production should be followed in order to gain sufficient insight into the process. These times are flexible and can be adjusted if needed.

Following the full video production throughout the WP will help untangle the creative process as performed by industry professionals when developing effective health science communication. The study will be guided by the creative process stages (CPS) model with its 17 stages that make up the artistic creative process [41]. This enables the study of the creative process at the macro level (the main stages) and micro level (the thinking underlying the stages) and takes an ecological approach: observation in the natural environment while the creative work is unfolding. This enables a direct, rich, and inexpensive assessment of the creative process, and the method has high ecological validity [41]. Based on the CPS model, WP2 will involve deductive development of a methodology for visualizing creative processes, so as to be able to capture, analyze, and visually present the multidimensional and intertwined aspects and stages involved in creative communication work.

#### Recruitment and Sampling

Participants will be recruited through the project’s consortium members and its wider network, as well as through project members’ own networks, including Stavanger University Hospital, Center for Developing Institutional and Home Care Services Sogn and Fjordane, Norwegian Institute of Public Health, Dagbladet, Anorak, Bulldozer Film, and Nordic Screens. Gender balance will be taken into account in the recruitment process, along with age, educational background, and occupation. All interviews and observation studies will be carried out virtually using Zoom.

### Phase 3: Evaluating the Communication’s Effect (WP3)

Building on the work in WP1 and WP2, WP3 will involve quantitative experiments to assess the effect of various factors related to audiovisual public communication of health science in general and pandemics in particular.

#### Scoping Review

First, in WP3, we will conduct a scoping review focusing on the recipients of the communication. We will search 3 main databases for public health, social sciences, and biomedical studies: PubMed, Scopus, and Embase. The search string will be designed based on the PCC (Population-Concept-Context) framework as recommended by the Johanna Briggs Institute Manual for Evidence Synthesis and scoping reviews [42] as a less restrictive alternative to the PICO (population, intervention, comparator, and outcome) mnemonic recommended for systematic reviews. The scoping review is expected to provide a comprehensive view of the state of the art and give insight about characteristics of recipients and how they can impact the outcomes of health video communication. The knowledge will contribute to the interpretation of findings from the WP’s experimental studies described in the following sections.

#### Randomized Controlled Trials

In WP3, we will perform 2 RCTs with a factorial between-subjects experimental design including various factors related to the video communication. The first RCT will assess nonvisual factors in health communication videos such as the effect of the video super of the presenter (ie, whether the person on screen is labeled as “Professor” or “Citizen” in the text at the bottom of the screen) or whether the message presented is neutral or includes a “call to action” (ie, whether the presenter merely delivers factual information or also encourages the viewer to act). The final choice of nonvisual factors will be informed by work in the preliminary phases of the project. Assessing the effect of such nonvisual factors will be done by having an actor recite different scripts to the camera. The second RCT will use the videos developed by professional video creators in WP2.

The videos will be screened for representativeness of the population. After consent, participants will be randomized to different videos and between-factors conditions. A link will lead them to a web page where the procedure is explained. For the first RCT, this web page differs according to ascribed Source and Messenger, Content, and Engaging factors. Participants will then be shown the video(s), followed by the questionnaires. Here, we focus not only on learning outcomes and the understanding of risk at a conceptual level but also on attitudes toward the subject, behavioral change, and compliance with the message. Gender, cultural background, age, education, and work variables will be entered as covariates in the statistical analyses and in targeted subgroup analyses.

All data collection in WP3 will be conducted online, using online surveys (Survey Monkey) and collaborative tools. With a fully digital and completely automated random-number generator and allocation procedure, video link submission and measurement instruments can be performed automatically, keeping the process free from experimenter input.

Both RCTs foresee the possibility of a longitudinal study through a follow-up survey aiming to assess whether communication outcomes (eg, learning, attitudes) persist over time, evaluate the motivation of participants to rejoin the study based on the video alternative they have been exposed to, and explore whether communication outcomes are influenced by the evolution of the COVID-19 pandemic (eg, vaccination coverage, recent infection trends).

#### Real-Life Observational Study

Based on the RCTs, the videos used in the experiments will go through mild editing and then be screened for audiences on a mass scale, tracking spread and exploring engagement metrics such as likes and comments. This will be done in collaboration with consortium partners (eg, the national newspaper, Dagbladet, and video influencer network, Nordic Screens). Here, success criteria will be assessed through strategies such as tracking of how much of a video the viewers watch before skipping, likes, sharing, and response rates to “click here for more” links and coupled with demographic data.

#### Recruitment and Sampling

Participants for the RCTs will be recruited through invites from consortium partners such as the Norwegian Air Ambulance Foundation (NAAF). Statistical power depends on a number of factors. For the first RCT, a power analysis in G*Power [43] assuming a medium effect-size (f^2^≥0.25) and a full factorial design with 5 covariates in an analysis of covariance (ANCOVA) yields a conservative sample size of 401 to achieve a statistical power of 95%. For the second RCT, a smaller sample size is needed, as there are fewer covariates. The NAAF database of financial supporters consists of approximately 150,000 people from the general public, and recruitment of only a small fraction of them (1%) will thus suffice for the intended power.

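### The stated effect size for the first RCT, f² ≥ 0.25, does not give the stated 401 participants at 95% power; f = 0.25 was probably meant

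*Protocol article*

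**What the plan says.** The Recruitment and Sampling section under Phase 3 (WP3) of the protocol article describes a G*Power calculation for the first RCT, "assuming a medium effect-size (f^2^≥0.25) and a full factorial design with 5 covariates". The test is an ANCOVA, and the calculation "yields a conservative sample size of 401" at 95% power. For the second RCT the section says only that fewer participants are needed because there are fewer covariates; it gives no number.

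The Randomized Controlled Trials section is consistent with five covariates: "Gender, cultural background, age, education, and work variables will be entered as covariates in the statistical analyses". On the design of the first RCT, it says that "this web page differs according to ascribed Source and Messenger, Content, and Engaging factors". It gives two examples of nonvisual factors, each with two levels: the on-screen label of the presenter, and whether the message includes a call to action. The final choice of factors is left to the earlier phases. The article does not state alpha, the numerator df of the powered test or the number of cells.

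**The concern.** G*Power's ANCOVA routine takes f, and the conventional medium value is f = 0.25. The article attaches that number to f². The two readings differ by a factor of four on the f² scale: 0.25 / 0.25² = 0.25 / 0.0625 = 4. For a two-level factor with equal groups, d = 2f, so the printed value means d of at least 1.0, against d = 0.5 for f = 0.25.

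This is the only quantified power claim for either RCT. If the printed effect size is wrong, a reader cannot tell which effect the trial was sized to detect, and cannot reproduce 401 from the stated inputs.

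**Working it through.** **Inputs from the article:** effect f² = 0.25 (the lower bound printed), 5 covariates, power 0.95, N = 401, fixed-effects ANCOVA in G*Power.

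**Inputs assumed, because the article does not give them:** alpha 0.05; numerator df (df1) from 1 to 31; number of groups g as shown below.

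**Formulae:** noncentrality λ = f²·N; df2 = N − g − 5; power = P[F′(df1, df2, λ) > F(0.95; df1, df2)]. The required N is the smallest that gives power of at least 0.95.

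**Step 1. Try to reproduce 401 as printed (f² = 0.25), and compare with f = 0.25.**

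| df1 | Groups | N at f² = 0.25 (f = 0.5) | N at f = 0.25 (f² = 0.0625) | Power at N = 401, f² = 0.25 | Power at N = 401, f = 0.25 |
|---|---|---|---|---|---|
| 1 | 8 | 55 | 210 | >99.9% | 99.9% |
| 3 | 4 | 74 | 279 | >99.9% | 99.3% |
| 7 | 8 | 96 | 357 | >99.9% | 97.2% |
| 10 | 11 | 108 | 400 | >99.9% | 95.1% |
| 10 | 32 | 111 | 401 | >99.9% | 95.1% |
| 15 | 16 | 126 | 459 | >99.9% | 91.0% |
| 31 | 32 | 169 | 599 | >99.9% | 77.1% |

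Example, first row: with N = 55, λ = 0.25 × 55 = 13.75 and df2 = 55 − 8 − 5 = 42. The critical F is 4.07 and power is 95.2%. With N = 54, power is 94.8%.

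The printed inputs do not reach 401 in any row. A much stricter alpha does not rescue them: alpha 0.001 with 31 df and 32 groups needs 258. At alpha 0.05 and 1 df, reaching 401 would take about 394 cells, which is not a credible factorial design.

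**Step 2. See what gives 401.** With f = 0.25, 10 df and 32 groups, N = 401 gives λ = 0.0625 × 401 = 25.06, df2 = 401 − 32 − 5 = 364, and power 95.05%. N = 400 falls just short (94.996%). With 11 to 27 groups the answer is 400.

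**Step 3. Check whether that solution is unique.** It is not. Other inputs come close: f = 0.18 with 1 df gives 404; f = 0.25 with 7 df at alpha 0.025 gives 404; f = 0.25 with 4 df at alpha 0.01 gives 397.

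**Step 4. Solve for the effect detectable with 401 at 95% power.** This gives f² = 0.033 (f = 0.18) at 1 df, 0.055 (f = 0.24) at 7 df and 0.095 (f = 0.31) at 31 df. All lie well below 0.25. At 1 df with a two-level factor, d = 2 × 0.18 = 0.36.

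**The case against.** The best reply is that this is a slip of notation with little consequence. The same sentence calls the effect medium, and both that word and the size of N point to f. A statistician would probably read it that way. At alpha 0.05, N = 401 meets the 95% target under either reading for tests with up to 10 df. All of this stands, and it limits the severity. It does not make the printed value right, and nothing elsewhere in the article corrects it.

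A second reply is that a journal article may leave alpha, df and cell counts to the full protocol or SAP. That also stands: their absence is not the finding. The finding is that a stated input conflicts with the stated result across the plausible designs.

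Three stronger readings are tempting, and the article does not support them:

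- **That 401 can come only from f = 0.25 with 10 df.** The 10 df is back-solved. No 10-df effect is described, the levels of the factors are not all fixed, and Step 3 shows other inputs that land close.
- **That the first RCT is too small.** At f = 0.25, power is at least 95% for effects with up to 10 df. It falls below that only for tests with more df, and the article names none.
- **That the second RCT will be underpowered.** Sizing it on the literal f² = 0.25 would give 55, 96 or 108 participants (1, 7 or 10 df), with 44%, 35% or 33% power for a true f = 0.25. But the article does not say that it will be sized this way. It also speaks of recruiting about 1% of roughly 150,000 supporters, or 0.01 × 150,000 = 1,500 people.

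**Conclusion.** The power statement is wrong as printed. With f² = 0.25, the required sample is about 55 to 169 over numerator df 1 to 31, not 401, and 401 would give more than 99.9% power rather than 95%. The probable cause is that f was written as f², which overstates the effect fourfold on the f² scale. This remains a probable explanation because the actual G*Power inputs are not given.

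The figures rest on an assumed alpha of 0.05, 5 covariates, and designs of up to 32 groups. The incompatibility does not depend on the exact choice of these; the match of f = 0.25 to 401 does. The severity is moderate: a stated power figure needs correcting, but neither the sample size nor the design is shown to be inadequate.

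**What to change.** Retrieve the G*Power output. Replace the printed effect size with the value that was entered (probably f = 0.25, f² = 0.0625), and report beside it the alpha, numerator df and number of groups actually used, so that 401 can be checked. Do not insert 10 df or alpha 0.05 unless the output shows them.

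Name the effect that was powered. If the effects of interest are 1-df main effects of two-level factors, restate the claim as follows: 401 participants give 95% power for about f = 0.18 (d = 0.36) at alpha 0.05. This is more informative than the present wording, because f = 0.25 would need only 210 for such an effect.

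The cost is one revised sentence and a look at the saved calculation. No extra participants are needed.

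### The second RCT is said to need fewer participants because it has fewer covariates, but dropping covariates saves at most about one participant in the ANCOVA power calculation

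*Protocol article*

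**What the plan says.** Under Recruitment and Sampling for Phase 3 (WP3), the article reports a G*Power analysis for the first RCT, "assuming a medium effect-size (f^2^≥0.25"), with "a full factorial design with 5 covariates in an analysis of covariance (ANCOVA"). This "yields a conservative sample size of 401 to achieve a statistical power of 95" percent.

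The second RCT is then sized relative to the first in one sentence: "For the second RCT, a smaller sample size is needed, as there are fewer covariates". The article gives no N, effect size, number of cells, numerator df or number of covariates for it.

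Under Randomized Controlled Trials, the two trials are introduced together: "we will perform 2 RCTs with a factorial between-subjects experimental design including various factors". The same section later says: "Gender, cultural background, age, education, and work variables will be entered as covariates in the statistical analyses and in targeted subgroup analyses". Five covariates are named there, the same number as in the power analysis for the first RCT, and the sentence does not restrict them to that trial.

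**The concern.** The sentence works as a sample-size rule: it tells the team that the second RCT may be smaller than 401, and why. In a fixed-effects ANCOVA power calculation, N is set by the effect size, alpha, the target power and the numerator df of the test. The number of covariates enters only through the denominator df, which at several hundred participants hardly matters.

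If the team acted on the sentence and cut the second RCT noticeably, the reduction would rest on no valid calculation. This is the trial that tests the professionally produced WP2 videos, so its size should come from its own design.

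**Working it through.** **Inputs.** From the article: power 95%, five covariates, N = 401 for the first RCT, and an effect size printed as f² ≥ 0.25 and called medium. Not in the article, so assumed: alpha 0.05, and a range of numerator df and cells. Because the printed effect size is ambiguous, both readings were run: f = 0.25 (f² = 0.0625) and f² = 0.25 taken literally.

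**Formula.** For N participants, k cells, c covariates and numerator df u:

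- noncentrality λ = f² × N
- denominator df v = N − k − c
- power = P[F′(u, v, λ) > F(0.95; u, v)], where F′ is the noncentral F

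The required N is the smallest with power of at least 0.95. The covariate count c appears only in v.

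**Reproducing 401.** The stated inputs do not fix N, since alpha, u and k are missing. With f = 0.25, alpha 0.05 and five covariates, the result comes to 401 at u = 10: 400 for the designs tried with 11 to 27 cells, and 401 for those with 32 to 54 cells. Read literally, f² = 0.25 gives 55 (u = 1) to 235 (u = 63, 64 cells), well short of 401. The figure therefore fits f = 0.25, but the check below was done under both readings.

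**Varying only the number of covariates.**

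| Effect size | u | Cells | N, 0 covariates | N, 5 covariates |
|---|---|---|---|---|
| f = 0.25 | 1 | 8 | 210 | 210 |
| f = 0.25 | 3 | 4 | 279 | 279 |
| f = 0.25 | 7 | 8 | 357 | 357 |
| f = 0.25 | 10 | 11 | 400 | 400 |
| f = 0.25 | 10 | 32 | 400 | 401 |
| f = 0.25 | 15 | 16 | 459 | 459 |
| f² = 0.25 | 7 | 8 | 95 | 96 |

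Across the designs tried with up to 64 cells, the largest saving from dropping all five covariates is one participant. Put as power: at N = 401, f = 0.25, u = 15 and 16 cells, v is 401 − 16 − 5 = 380 with five covariates and 385 with none, and power is 0.9100 and 0.9102.

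**What does move N.** At f = 0.25, N is 210, 279, 357 and 400 for u = 1, 3, 7 and 10.

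**If the dropped covariates are prognostic.** Suppose the five together explain a share R² of the within-cell outcome variance. R² is an assumption, as the article gives none. Leaving them out turns f² into f² × (1 − R²) for the same raw effect. With u = 10, 32 cells and no covariates:

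- R² = 0.10: f² = 0.0625 × 0.90 = 0.05625, N = 444 (approximation 401 / 0.90 = 446)
- R² = 0.20: f² = 0.0625 × 0.80 = 0.0500, N = 498 (approximation 401 / 0.80 = 501)

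**The case against.** The strongest reply is that the conclusion may be right even though the reason is not. The second RCT compares produced videos and may have fewer factors or levels than the first. If so, its numerator df is smaller and a smaller N follows, as the figures for u show. The word covariates may even have been meant loosely for factors. This stands as a possibility. It does not rescue the sentence, which names covariates as its reason, and the article does not give the second RCT's factor structure.

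Four stronger readings are tempting, and the document does not support them:

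- *The stated direction is backwards.* In the calculation cited, with a fixed standardised effect, fewer covariates give the same N or one fewer. The sign is right and the size negligible. The direction reverses only for a fixed raw effect when prognostic covariates are dropped, and the R² needed for that is assumed.
- *The second RCT will miss its intended power.* No N is stated for it, so there is no shortfall to compute.
- *The second RCT carries the main hypotheses.* The Introduction does not assign its hypotheses to either trial. The first RCT also varies content through different scripts.
- *Both RCTs must use all five covariates.* A general sentence in a condensed article lists five for the analyses. That is a tension with fewer covariates in the second RCT, not proof that the same set applies to both.

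The practical exposure is also limited. The article says "recruitment of only a small fraction of them (1%) will thus suffice for the intended power", and 1% of about 150,000 is 1,500, well above 401.

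**Conclusion.** The narrow point holds. The only reason given for a smaller second RCT is not valid: going from five covariates to none changes the required N by at most 1 in the designs tried. This rests on the fixed-effects ANCOVA F test, 95% power and an assumed alpha of 0.05. It holds for both readings of the effect size and for every numerator df and cell count tried up to 64 cells.

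Whether the second RCT would in fact be too small cannot be decided from the article. The fault is a wrong sample-size rule, not a demonstrated loss of power. It should be corrected because the rule would govern the size of a trial and is cheap to put right.

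**What to change.** 1. Delete the covariate rationale for the second RCT.
2. Give that trial its own power statement at 95%: effect size (written unambiguously as f or f²), alpha, number of cells, numerator df of the smallest test that must be powered, and the resulting N. A value below 401 is acceptable if these inputs produce it, but not merely because covariates are fewer.
3. State which covariates each RCT uses, so that Recruitment and Sampling agrees with the list of five under Randomized Controlled Trials.

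The cost is one sentence and one G*Power run. Recruitment is not strained: even at 401 in each trial, 2 × 401 = 802, about 0.5% of 150,000 and inside the roughly 1,500 that the article's 1% implies.
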